### Data management {19}

*Data validation and quality control*: Implement rigorous data validation and quality control procedures. This includes real-time validation checks during data entry to identify errors, inconsistencies, or missing values. Conduct routine data audits to ensure accuracy and integrity. Develop a clear protocol for resolving discrepancies and data outliers. Maintaining high data quality enhances the reliability and validity of research outcomes.*Documentation and version control*: Maintain comprehensive documentation of the data management process. Document data collection procedures, data cleaning processes, and any changes made to the dataset. Establish version control to track dataset modifications over time. This documentation not only ensures transparency but also assists in reproducibility and future analyses.

### Confidentiality {27}

Prioritize data security and privacy throughout the data management process. Implement encryption measures to protect sensitive participant information during transmission and storage. Each participant will be assigned an identification number to be stored in place of their real name. Establish strict access controls to limit data access to authorized personnel only. Regularly update and patch software to mitigate vulnerabilities.

### Plans for collection, laboratory evaluation and storage of biological specimens for genetic or molecular analysis in this trial/future use {33}

This trial does not involve the collection of biological samples for genetic or molecular analysis.

## Statistical methods

### Statistical methods for primary and secondary outcomes {20a}

Statistical analysis was conducted according to intention-to-treat (ITT). The chi-square test was used to analyze categorical variables when comparing baseline demographic and clinical characteristics; For continuous variables, we first performed exploratory data analysis and Shapiro–Wilk tests to determine the normality of our data distribution, using independent *t* tests when the results conform to a normal curve and non-parametric rank sum tests when they do not.

To analyze the data, we will employ repeated measures analysis of variance (RM-ANOVA) as the statistical method. Our primary interest lies in comparing the changes over time between the intervention and control groups at baseline, 4 weeks, and 16 weeks. We will utilize repeated measures ANOVA to examine the main effects between the two groups while considering the factors of time and group. As part of the analysis, multiple comparisons will be performed, including comparisons between baseline and 4 weeks, baseline and 16 weeks, and 4 weeks and 16 weeks. These comparisons will help identify significant differences across different time points. To assess statistical significance, appropriate statistical indicators such as *F*-values and *p*-values will be utilized. In case of significant differences, post hoc multiple comparison analyses will be conducted to determine specific time points of significance. Finally, descriptive statistics and appropriate graphical representations will be employed to illustrate the overall trends and changes in the data. Statistical analyses were done using the SPSS software for Windows, version 23.

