#### Outcomes {12}

### Primary outcome

The primary outcome is the mean pain intensity over the previous week assessed using an 11-point numeric rating scale (NRS;0 = no pain, 10 = unbearable pain) at 16 weeks after randomization. A higher score indicates higher pain intensity [25]. The between-group minimal clinically important difference (MCID) is 1.0 point on the NRS scale [26]. The within-group MCID is a 30% change from baseline [27].

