### Sample size {14}

With a non-inferiority design, the intervention group and control group had a 1:1 ratio of participants. In March 2023, we conducted a pilot study in the outpatient department of the First Affiliated Hospital of Sun Yat-sen University and collected a total of 21 subjects, including 15 in the intervention group and 6 in the control group, for a 4-week intervention. They were followed up 3 months later. The result yielded mean decreases of − 1.6 (SD = 2.0) for the intervention group and − 1.9 (SD = 1.9) for the control group on the NRS. With a significance level (*α*) of 0.05 and a power (1-*β*) of 0.9, considering a non-inferiority margin of − 1 and a difference (*δ*) of 0.3 in NRS decrease between the intervention and control groups, the PASS software (version 21) estimated that each group required 41 participants. Assuming a dropout rate of 20%, a total of at least 102 participants were needed for both groups.

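### The Shapiro–Wilk rule for choosing a t test or rank-sum test is not confined to baseline data, and neither it nor the RM-ANOVA guarantees a between-group mean NRS difference to set against the 1-point margin

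*Protocol article*

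**What the plan says.** All of the analysis text sits in the protocol article under Statistical methods for primary and secondary outcomes {20a}.

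- The first paragraph opens with categorical data: "The chi-square test was used to analyze categorical variables when comparing baseline demographic and clinical characteristics". After a semicolon the same sentence continues: "For continuous variables, we first performed exploratory data analysis and Shapiro–Wilk tests to determine the normality of our data distribution". It then prescribes independent t "tests when the results conform to a normal curve and non-parametric rank sum tests when they do not".
- The second paragraph names RM-ANOVA, for data from the baseline assessment and the follow-ups in weeks 4 and 16, in these words: "as the statistical method. Our primary interest lies in comparing the changes over time between the intervention and control groups". It adds: "We will utilize repeated measures ANOVA to examine the main effects between the two groups while considering the factors of time and group".
- The pairwise comparisons listed are baseline with 4 weeks, baseline with 16 weeks, and 4 with 16 weeks. Post hoc comparisons follow only where a significant difference is found.
- The decision statistics are introduced with "To assess statistical significance, appropriate statistical indicators such as" and are F and p values.

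Elsewhere, the Primary outcome section says that pain is "assessed using an 11-point numeric rating scale" running from 0 to 10, and the eligibility criteria exclude scores below 4. Sample size {14} builds the trial on mean NRS decreases, "considering a non-inferiority margin of" −1.

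**The concern.** A non-inferiority claim on a mean scale needs three things: an estimate of the between-group mean difference, a confidence limit for it, and a comparison of that limit with the margin. The analysis section does not provide this by either of its routes.

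The first route is the normality rule. It stands under a heading about outcomes and its clause on continuous variables carries no limit of its own. An analyst who needs a two-group comparison of NRS change at a single time point could reasonably apply it. NRS scores are whole numbers, so ties alone make Shapiro–Wilk reject often, and the rule then sends the comparison to a rank-sum test. That test gives a p value for a shift in ranks. It gives no difference in NRS points.

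The second route is the RM-ANOVA. It is not conditional on normality, but as described it ends in F and p values and in comparisons between time points. A non-significant F test does not show non-inferiority.

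At stake is whether the trial, analysed as written, can answer the question it was sized for.

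**Working it through.** **1. The design figure.** Inputs from Sample size {14}: margin 1, difference 0.3, SDs 2.0 and 1.9, alpha 0.05 (sidedness not given), power 0.9. With SD 2.0, one-sided alpha 0.05 and a distance to the margin of 1 + 0.3 = 1.3:

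n per arm = 2 × SD² × (z₀.₉₅ + z₀.₉₀)² / distance² = 2 × 4 × (1.645 + 1.282)² / 1.69 ≈ 40.5, rounded up to 41.

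This reproduces the stated 41. Dropout: 41 / 0.8 = 51.25, so 52 per arm and 104 in all, as in the Abstract. The design is therefore a comparison of two means against a margin in NRS points. (The pilot difference runs against the intervention, so whether the distance should be 1.3 or 0.7 is a separate matter and is not used here.)

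**2. How often the rule would select the rank-sum test.** Simulation, 3,000 trials per setting, Shapiro–Wilk at 0.05. From the article: mean changes −1.6 and −1.9, SDs 2.0 and 1.9, an entry floor of 4 and a 0–10 scale. Assumed: normal values rounded to whole points and, for the truncated model, a baseline of N(5.5, 1.5). Cells give the percentage rejecting with 41 / 52 per arm.

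| Data model | One given arm | At least one arm | Arms pooled |
|---|---|---|---|
| Change, normal, rounded only | 29 / 41 | 54 / 68 | 78 / 94 |
| Change, entry floor 4, follow-up clipped to 0–10 | 33 / 45 | 60 / 77 | 89 / 99 |
| Continuous normal (reference) | 5 / 5 | 10 / 10 | 5 / 4 |

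Repeat runs under similar assumptions gave 50–62% (41 per arm) and 66–78% (52 per arm) for at least one arm. The article does not say whether the test is run by arm or on pooled data, so all three columns are shown. The reference row shows that whole-number scoring alone is enough to drive most of the rejections.

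**3. What the t-based interval does on the same data.** In 4,000 trials per setting under the truncated model, the ordinary 95% interval for the mean difference covered the true value in 94.1% (41 per arm) and 94.6% (52 per arm). Failing Shapiro–Wilk is thus no reason to give up the mean difference.

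**4. What the RM-ANOVA delivers.** A group main effect averages over all three time points, including baseline. Suppose there is no baseline difference and a true deficit of exactly 1 point at both follow-ups. The main effect is then (0 + 1 + 1) / 3 = 0.67, so even an interval for it could not be read against a margin of 1. The three listed pairwise comparisons contrast times, not groups. The post hoc step depends on a significant result, which a trial with similar arms would often not produce.

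**The case against.** The strongest reply is that the normality rule is simply the usual description of a baseline table. One sentence pairs chi-square for categorical variables with t or rank-sum tests for continuous ones, and the baseline phrase is in its first half. Confining that phrase to chi-square would leave continuous baseline variables without a stated test. The text then changes tense and paragraph and names RM-ANOVA for the trial data. This is the more natural reading and it stands. It does not settle the matter, because neither the heading nor the clause on continuous variables carries the limit.

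It may also be said that such detail belongs in a statistical analysis plan that is not shown. That would answer a complaint about omission. Here the article states a test-selection rule without a limit and states F and p values as the basis for judgement.

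Several stronger inferences are tempting and are not supported:

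- *That the gated rule is the only two-group test named.* RM-ANOVA has a group factor and no normality gate.
- *That pre-testing distorts the error rate.* In 4,000 simulated trials per setting under the truncated model with no true difference, the gated procedure rejected in 4.9% (41 per arm) and 5.0% (52 per arm), against 4.8% and 5.0% for the t test alone. With rounded normal data it was 5.2% and 5.6%, against 5.0% and 5.4%. There is no material inflation.
- *That the rank-sum test in particular misses a 1-point deficit.* At that deficit it gave p of 0.05 or more in 40% (41 per arm) and 28–30% (52 per arm) of trials, but a t test gave about 37–38% and 26–28%. This is the ordinary power of a difference test. It shows only that no difference p value can decide non-inferiority.
- *That the rule governs outcomes measured once, such as satisfaction and attendance.* The article does not say how often these are measured, and the content of Table 1 is not available here.

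**Conclusion.** The point holds in a limited form. The Shapiro–Wilk rule probably belongs to the baseline table but is not restricted to it. If it were applied to NRS change, a rank-sum test would be selected in about 50–60% of trials with 41 per arm and 66–78% with 52 per arm, counting failure in either arm. Counting one given arm gives 29–45%. These rates rest on rounded normal data, with an assumed baseline distribution in the truncated case.

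The more important part does not depend on how the rule is read. Nothing in the analysis section sets a between-group mean difference and its confidence limit against the 1-point margin. The rank-sum test cannot do so, and the RM-ANOVA as described does not. The wording should be corrected before analysis.

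**What to change.** In Statistical methods {20a}:

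1. State that the Shapiro–Wilk, t test and rank-sum rule applies only to the comparison of baseline characteristics.
2. State that for the NRS the between-group difference in mean change at the primary time point will always be reported with its confidence interval, whatever the normality result, and that non-inferiority will be concluded only if the interval excludes a deficit of 1 point. The interval's level should match the alpha of the sample size: one-sided 0.05 corresponds to a two-sided 90% interval, one-sided 0.025 to 95%.
3. Optionally, add a bootstrap interval for the mean difference as a sensitivity analysis if non-normality is a worry.

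The primary time point has to be settled first, since the Abstract gives change to 4 weeks and the Primary outcome section gives 16 weeks. The RM-ANOVA can stay as a supporting description of the time course. The cost is a few sentences, with no extra patients, visits or data.

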## Abstract

**Background:**

Core stability exercise (CSE) is a globally acknowledged intervention for managing chronic low back pain. However, the sustained adherence of patients with chronic low back pain to CSE can be challenging, mainly due to the absence of supervision and guidance from physical therapists during home-based exercise sessions. Consequently, exercise compliance tends to decline, resulting in suboptimal long-term effectiveness of the intervention. In this trial, our primary aim is to evaluate the potential therapeutic equivalence between home-based rehabilitation training employing key point identification technology and exercise guidance administered in a hospital setting.

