**Discussion:**

If home-based rehabilitation method is demonstrated to be non-inferior or even superior to traditional face-to-face exercise guidance, it could significantly advance the adoption of digital medical care and contribute to improving the overall health of the population.

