### Trial design {8}

We are planning to conduct a randomized controlled non-inferiority clinical trial. Eligible participants will be randomly allocated in a 1:1 ratio into either the experimental group or the control group. The experimental group will undergo home rehabilitation training with guidance from human key point detection technology, whereas the control group will receive exercise instruction in a hospital setting. The trial protocol will adhere to the Standard Protocol Items: Recommendations for Interventional Trials (SPIRIT 2013) guidelines for conducting and reporting clinical trials [20].

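### The stated analysis (RM-ANOVA F- and p-values) tests for no difference and never uses the 1-point margin, so it does not match the non-inferiority design

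*Protocol article*

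**What the plan says.** Trial design {8} states: "We are planning to conduct a randomized controlled non-inferiority clinical trial". The abstract's Discussion gives the conclusion sought: that home training is "demonstrated to be non-inferior or even superior to traditional face-to-face exercise guidance". Sample size {14} supplies the margin ("considering a non-inferiority margin of" −1), which equals in size the between-group MCID under Primary outcome: "The between-group minimal clinically important difference (MCID) is 1.0 point on the NRS scale".

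Statistical methods {20a} then says: "To analyze the data, we will employ repeated measures analysis of variance (RM-ANOVA) as the statistical method". It describes main effects of group and time over baseline, 4 weeks and 16 weeks. Significance is to be judged by indicators such as F- and p-values, with post hoc comparisons of time points if differences are significant. It gives no non-inferiority hypothesis, no confidence interval for the group difference and no reference to the margin.

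The aim is worded in more than one way. In the abstract, "our primary aim is to evaluate the potential therapeutic equivalence between home-based rehabilitation training" and hospital guidance is the question. Objectives {7} speaks of comparable effects.

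**The concern.** A non-inferiority claim needs evidence against the hypothesis that the new treatment is worse by at least the margin. The analysis in {20a} tests a different hypothesis, that the groups do not differ. A non-significant F test may reflect similar groups or merely imprecise data. A significant one has no direction in itself, and even a significant deficit can lie wholly inside the margin. So neither result of the stated test answers the question in {8}, and the sample size in {14} was calculated for a margin comparison that {20a} does not describe.

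The primary conclusion is at stake. If the rule for declaring non-inferiority is settled only once data are in hand, it is open to bias. If it defaults to an absence of significance, noisy or incomplete data make success more likely.

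**Working it through.** **1. Inputs.** All are from Sample size {14} unless noted.
- SD of NRS change: 2.0 (intervention) and 1.9 (control)
- Margin: 1 point; difference: 0.3
- Alpha 0.05, with no statement of one- or two-sided; power 0.90
- Evaluable per group: 41
- Randomised per group: 52 (abstract, Methods)

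**2. Reproducing the plan's own figure.** The formula is n = 2 × SD² × (z₁₋α + z₀.₉₀)² / d², with SD 2.0 and d = 1 + 0.3 = 1.3.
- One-sided 0.05: 2 × 4 × (1.645 + 1.282)² / 1.69 = 40.5, so 41 (42 with the t distribution).
- One-sided 0.025: 2 × 4 × (1.960 + 1.282)² / 1.69 = 49.7, so 50.

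The stated 41 is therefore a margin-based calculation at one-sided 0.05. That level is an inference from the result; {14} does not say it. The match also needs the 0.3 to count in the intervention's favour, although the pilot decreases (1.6 against 1.9) favour control. That is a separate issue.

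**3. Design set against analysis.**

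| Element | Design ({8}, {14}) | Analysis ({20a}) |
|---|---|---|
| Null hypothesis | Intervention worse by the margin or more | No difference |
| Margin | 1 NRS point | Not used |
| Direction | One side | None (F test) |
| Decision quantity | Confidence limit or shifted test | F- and p-values |

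**4. Illustration of the mismatch.** Assume, hypothetically, that p > 0.05 were taken as showing comparable effects. The test is a two-sample t test on change, two-sided 0.05, with SE = √((2.0² + 1.9²)/n).
- n = 41: SE = √(7.61/41) = 0.431
- n = 52: SE = √(7.61/52) = 0.383

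The probability of a non-significant result comes from the noncentral t distribution with noncentrality equal to true deficit / SE:

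| True deficit | n = 41 per group | n = 52 per group |
|---|---|---|
| 1.0 point (at the margin) | 1.0/0.431 = 2.32, giving 37% | 1.0/0.383 = 2.61, giving 26% |
| 1.3 points | 1.3/0.431 = 3.02, giving 15% | 1.3/0.383 = 3.40, giving 8% |

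At a true deficit of 1.0, comparing the confidence limit with the margin holds the false claim at 5% (one-sided 0.05) or 2.5% (one-sided 0.025).

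**5. Where the two rules disagree.** With 41 per group the 95% half-width is 1.990 × 0.431 = 0.86 and the 90% half-width is 1.664 × 0.431 = 0.72. An observed deficit between 1 − 0.72 = 0.28 and 0.86 would be non-significant yet would fail non-inferiority on a 90% interval. The pilot's 0.3 in favour of control lies inside that range. With 52 per group the range is about 0.36 to 0.76.

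**6. RM-ANOVA itself.** The t test above stands in for the stated method. A simulation used three visits, compound symmetry, a 1.0-point deficit at both follow-ups and assumed between-visit correlations of 0.3 to 0.7. The group-by-time interaction was non-significant in about 23% (n = 52) to 34% (n = 41) of trials. The group main effect, which averages in the baseline visit, was non-significant in 20% to 74%, depending on the correlation and group size. The article gives no correlation, so no single RM-ANOVA figure can be fixed.

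**The case against.** The strongest defence is that this is a condensed article whose SAP is not shown. The fitted model can yield a between-group difference with a confidence interval, the wording about indicators in {20a} is not an exclusive list, and the decision rule might sit in the SAP. This stands in part. A reader might infer that no margin comparison will ever be made, and the document cannot show that. But {20a} does not leave the method open: it describes a test of difference. A SAP that compared an interval with the margin would be supplying a primary analysis that the article does not describe.

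A reader might also infer that the trial will pass an inferior treatment in a quarter to a third of cases. The document does not support this. Nowhere does it say that p > 0.05 will be read as comparable, and the abstract makes its conclusion depend on non-inferiority being demonstrated. The percentages describe a hypothetical rule, a proxy test and a deficit exactly at the margin. They fall quickly for larger deficits, and the upper figure is 37%, not a third.

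Finally, *equivalence* and *comparable* can be read as lay descriptions, since {8} and {14} consistently say non-inferiority. That is fair: the wording is an editorial matter and adds nothing to the severity.

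**Conclusion.** The point holds in this form: the analysis stated in {20a} is a test of no difference that omits the margin in {14}. It does not match the design in {8}, and a non-significant result from it would not support the non-inferiority conclusion in the abstract. This rests on the text alone and needs no assumption about how p-values would be read. It must be corrected because it concerns the primary conclusion.

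The error rates in the working only illustrate why the distinction matters. They assume the pilot SDs, a t test on change and a decision rule that the article does not contain.

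**What to change.** 1. Reconcile the primary time point first. The abstract's Methods gives the change from baseline to 4 weeks; Primary outcome gives 16 weeks. The steps below cannot be carried out until one is fixed.
2. In {20a}, make the primary analysis the between-group difference in NRS change at that time point with its confidence interval. Declare non-inferiority only if the limit on the unfavourable side excludes a decrease 1.0 point smaller than control.
3. State in {14} and {20a} whether alpha is one- or two-sided. One-sided 0.05 corresponds to a two-sided 90% interval and reproduces the stated 41 per group. A 95% interval corresponds to one-sided 0.025 and does not match 41; the same inputs then give 50.
4. Test superiority only after non-inferiority has been shown. Keep the RM-ANOVA F tests as supportive.
5. Use non-inferiority in the aim and objective (editorial).

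The cost is wording in the protocol and, where one exists, the SAP. The analysis uses the same data and software. If the sidedness settled in step 3 is not the one that gives 41, the sample size must also be recalculated.

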**Methods:**

In this trial, we will randomly assign 104 adults with chronic low back pain (CLBP) to either an intervention or control group, with 52 participants in each group. Both interventions will consist of three weekly 0.5-h sessions of core stability exercise (CSE). The intervention group will engage in home rehabilitation training utilizing key identification technology for movement, while the control group will perform supervised exercises in a hospital setting. Outcome assessments will be conducted at 4 weeks and 16 weeks after randomization. The primary outcome measure will be the change in pain intensity based on numeric rating scale (NRS scores) from baseline to 4 weeks. Secondary outcomes will include changes in physical function (measured by the Oswestry Disability Index (ODI)) and lumbar spine mobility as well as activity participation and treatment satisfaction.

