### Methods for additional analyses (e.g., subgroup analyses) {20b}

We plan to classify the severity of each group of patients into severe pain and moderate pain according to the NRS and analyze whether there are differences in changes between them.

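### The only between-group effect the plan names, the RM-ANOVA group main effect, averages in the baseline NRS and estimates neither stated primary endpoint

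*Protocol article*

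**What the plan says.** The Trial design section describes a "randomized controlled non-inferiority clinical trial". The primary endpoint refers to a single follow-up visit in both places where it is given, though the two differ: the Abstract has "change in pain intensity based on numeric rating scale (NRS scores) from baseline to 4 weeks", while the Primary outcome section takes mean NRS over the previous week "at 16 weeks after randomization. A higher score indicates higher pain intensity".

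Section {20a} makes repeated measures ANOVA the method of analysis. It says that the primary interest is in "comparing the changes over time between the intervention and control groups at baseline, 4 weeks, and 16 weeks". The next sentence gives the effect to be examined: "We will utilize repeated measures ANOVA to examine the main effects between the two groups while considering the factors of time and group". The multiple comparisons that follow are between time points, "including comparisons between baseline and 4 weeks, baseline and 16 weeks, and 4 weeks and 16 weeks". For significance, "appropriate statistical indicators such as *F*-values and *p*-values will be utilized".

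So baseline is one of three response levels. The section mentions no baseline covariate, no group-by-time term and no contrast between the arms at a single visit.

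**The concern.** A group main effect in a repeated measures ANOVA is the difference between arms averaged over every level of time. One of the three levels here is measured before treatment, where randomised arms differ only by chance. Including it adds an expected zero to the average.

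Two things follow. The effect does not correspond to the primary endpoint in either of its versions. And it usually understates how much worse the home programme is. In a superiority trial such dilution costs power. In a non-inferiority trial it favours the conclusion that the trial hopes to reach.

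The listed pairwise comparisons do not repair this. As worded, they describe how pain changes from one visit to another, not how the arms differ at a visit.

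**Working it through.** **Notation.** d0, d4 and d16 are the expected NRS differences, intervention minus control, at baseline, week 4 and week 16. A positive value means that the intervention is worse.

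**Inputs from the protocol.** 1:1 randomisation (Trial design), so d0 = 0 in expectation. Margin 1 NRS point, 41 evaluable per group, α 0.05 with sidedness not stated, and pilot SDs of 2.0 and 1.9 for the NRS decrease (Sample size). Pooled change SD = √((2.0² + 1.9²)/2) = 1.95.

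**Assumed.** Equal correlation ρ between any two visits, from 0.3 to 0.7, and equal SD at each visit. The protocol gives neither.

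**The plan's own figure.** 2 × 2.0² × (1.645 + 1.282)² / 1.3² = 40.5, so 41 per group. The stated number reproduces at one-sided 0.05, and that level is used below. The 1.3 is the margin plus 0.3. Whether the 0.3 should be added is a separate question that does not affect this point.

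**Expected main effect.** (d0 + d4 + d16)/3 = (0 + d4 + d16)/3, which is 2/3 of (d4 + d16)/2 for any pattern. Against a single visit the loss depends on the pattern:

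| d4 | d16 | Main effect | Lost relative to d16 |
|---|---|---|---|
| 0 | 1.0 | 0.33 | two thirds |
| 0.5 | 1.0 | 0.50 | half |
| 1.0 | 1.0 | 0.67 | one third |
| 1.5 | 1.0 | 0.83 | one sixth |
| 2.0 | 1.0 | 1.00 | none |

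The same holds with the visits exchanged if week 4 is primary: d4 = 1.0 with d16 = 0 gives 0.33.

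**Simulation check.** With 400,000 per arm, ρ = 0.5 and a true deficit of 1.0 at both visits, the main effect came out at 0.66 and the baseline-adjusted week-16 difference at 1.00.

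**If the main effect were judged against the margin.** The true deficit is 1.0 at both visits, so a correct test declares non-inferiority in 5% of trials.

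- Visit SD σ = 1.95/√(2(1 − ρ)).
- SE of the main effect = σ × √((1 + 2ρ)/3) × √(2/n).
- P(non-inferiority declared) = Φ((1 − 0.667)/SE − 1.645).

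| ρ | σ | SE, n = 41 | False rate, n = 41 | False rate, n = 52 |
|---|---|---|---|---|
| 0.3 | 1.65 | 0.266 | 35% | 41% |
| 0.5 | 1.95 | 0.352 | 24% | 28% |
| 0.7 | 2.52 | 0.497 | 17% | 19% |

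The pilot SDs belong to the change, so σ has to move with ρ. Fixing 2.0 as the SD at each visit would give a narrower range, 21% to 27% with 41 per group.

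**Precision from adjustment.** The variance of a change score is 2σ²(1 − ρ). The residual variance after ANCOVA on baseline is σ²(1 − ρ²). The ratio is (1 + ρ)/2: 0.65, 0.75 and 0.85 for ρ = 0.3, 0.5 and 0.7.

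**The case against.** The strongest reply is that {20a} itself declares an interest in "comparing the changes over time between the intervention and control groups at baseline, 4 weeks, and 16 weeks". That is a group-by-time question, and baseline does not dilute a group-by-time term or a contrast of change scores. If such a term decides the trial, no deficit is hidden. This stands as far as it goes: the text does not say which term decides, and a reader should not infer that the trial is committed to a diluted primary result. But the aim and the named effect then disagree, and only the main effect is written down. An overall interaction F test would not settle it either, because it gives no signed difference at the primary visit.

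A second reply is that {20a} mentions only F- and p-values and never sets the main effect against the margin. That is correct. The false-declaration rates show what would happen if it were done; they are not a property of the written plan.

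A third is that an unadjusted comparison of change scores is valid under randomisation. That is also correct. Using baseline as a covariate adds precision. The error lies in using baseline as an outcome level within a main effect, not in the lack of adjustment.

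A reader might also extend the criticism to {20b}, which will "classify the severity of each group of patients into severe pain and moderate pain according to the NRS" and look for differences in change. The sentence can mean severe against moderate patients, or the two arms within each severity class. It is exploratory, and any figure for regression to the mean would need a baseline mean, SD and cut-off that the protocol does not give. The documents do not support a finding there.

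**Conclusion.** The point holds in a limited form. The plan's stated interest and its named between-group effect do not match. The named effect is expected to be two thirds of the mean post-baseline deficit and estimates neither version of the primary endpoint. This part is algebra and needs only randomisation.

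A reader might infer that every deficit shrinks by one third. That is exact only for the mean of the two follow-ups, or when both deficits are equal. For a week-16 deficit of 1.0, the loss in the cases worked runs from two thirds (no deficit at week 4) to nothing (a deficit of 2.0 at week 4).

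The false non-inferiority rate of about 17% to 35% rests on four conditions: the main effect is compared with the margin, the deficit is 1.0 at both visits, the change SD is 1.95, and the correlation lies between 0.7 and 0.3. Only the SD comes from the protocol. Every case in that range is well above 5%. The plan should be corrected, since the change costs almost nothing.

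**What to change.** In {20a}, replace the group main effect with one of these:

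- an ANCOVA of NRS at the primary visit, with group and baseline NRS in the model; or
- a mixed model for weeks 4 and 16 with group, visit, group × visit and baseline NRS as covariate, from which the group difference at the primary visit is taken.

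In both, baseline is a covariate and not an outcome level. Report the adjusted between-group difference at the primary visit with its confidence interval. This requires the Abstract and the Primary outcome section to agree on which visit is primary. The comparisons between time points can stay as description.

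The cost is a change of analysis wording. Baseline NRS is already collected, no extra visit or patient is needed, and SPSS, the named software, can fit either model. The change should be fixed before any outcome data are compared by arm, including at the planned interim analysis.
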